#### Visit 1: Screening (Upto Day-7)

- Written informed consent of the patient
- Demographic details & medical history
- General physical and systemic examination
- Concomitant diseases and medications

|                                                                                  |                                                                                                       |                                                              |
|----------------------------------------------------------------------------------|-------------------------------------------------------------------------------------------------------|--------------------------------------------------------------|
| [figure not shown] | Clinical trial to evaluate efficacy and safety of Amla Extract (AMX160) in patients with Dyslipidemia | Project No. AN-03ASE
0115H2-SYN02
Ver.01, Dt: 01-01-15 |
|----------------------------------------------------------------------------------|-------------------------------------------------------------------------------------------------------|--------------------------------------------------------------|

- Inclusion and exclusion criteria check
- Blood collection for laboratory tests (only TC, TG, LDL, HDL, VLDL, FPG, CBC, LFT, RFT, SPT will be analysed first; blood sample will be stored for further analysis); Urine R/M; ECG
- SPT in females of child bearing potential

#### Visit 2: Randomization (Day 0)

- Inclusion & Exclusion Criteria re-check
- General physical and systemic examination
- Laboratory investigations - If patient satisfies all inclusion and exclusion criteria, other investigations i.e. Apo A1, Apo B, hs CRP, TSH, Homocysteine CoQ10, HbA1c and HMG Coenzyme Reductase activity will be done utilizing the same blood sample as collected at time of screening. No fresh blood sample will be collected on this visit
- Randomization and dispensing of study medication
- Recording of concomitant diseases and medications
- Instructions for lifestyle modification (healthy diet with aerobic exercise at least 4 days a week)

#### Visit 3: Follow-up visit (Day 28 $\pm$ 5)

- General physical and systemic examination
- Study Medication count
- Adverse event recording
- Concomitant diseases and medications
- Blood sample collection for laboratory analysis
- Dispensing Study Medication
- Instructions for lifestyle modification (healthy diet with aerobic exercise at least 4 days a week)

#### Visit 4: Follow-up visit (Day 56 $\pm$ 5)

- General physical and systemic examination
- Study Medication count
- Adverse event recording
- Concomitant diseases and medications
- Blood sample collection for laboratory analysis
- Dispensing Study Medication
- Instructions for lifestyle modification (healthy diet with aerobic exercise at least 4 days a week)

|                                                                                  |                                                                                                       |                                                              |
|----------------------------------------------------------------------------------|-------------------------------------------------------------------------------------------------------|--------------------------------------------------------------|
| [figure not shown] | Clinical trial to evaluate efficacy and safety of Amla Extract (AMX160) in patients with Dyslipidemia | Project No. AN-03ASE
0115H2-SYN02
Ver.01, Dt: 01-01-15 |
|----------------------------------------------------------------------------------|-------------------------------------------------------------------------------------------------------|--------------------------------------------------------------|

#### Visit 5: End of Study visit (Day 84 $\pm$ 5)

- General physical and systemic examination
- Study Medication count
- Adverse event recording
- Concomitant diseases and medications
- Blood collection for laboratory investigations and SPT in females of child bearing potential, Urine R/M, ECG
- Overall tolerability evaluation

#### Unscheduled Visits

Unscheduled visits will be allowed any time during the study for assessment and management of AEs and any concurrent clinical conditions and the same shall be captured in the Unscheduled visit form.

### **8.1 Protocol violation, deviation, waiver or amendments**

During this study examples of deviations may include, but are not limited to:

- Participant seen outside window period ( $\pm$  5 days)
- Missed or incomplete study procedure (e.g. examination)

During this study following will be considered as protocol violations:

- Failure to report within  $\pm$  7 days
- Failure to obtain written informed consent
- Missing Informed Consent Form (ICF)
- ICF does not contain all the required signatures
- ICF used was not the current EC approved version
- Participant did not meet eligibility criterion
- Prescribed dosing outside protocol guidelines
- A breach of confidentiality
- Falsifying research or medical records
- Participant receives wrong treatment
- Randomization of participant prior to EC approval of protocol
- Subject withdrawal criteria not followed
- Use of prohibited concomitant treatments

Any deviation or violation from the Protocol should be duly explained with justification(s) thereof by the concerned investigator. The Investigator should promptly report to the Ethics Committee, sponsor's representative / medical expert, deviation / violation from the Protocol, if any which may cause immediate hazards to the subjects. There will be no protocol waiver in this study. Subjects dropped out before the study completion will not be replaced. Patients violating the Protocol will

|                                                                                  |                                                                                                       |                                                              |
|----------------------------------------------------------------------------------|-------------------------------------------------------------------------------------------------------|--------------------------------------------------------------|
| [figure not shown] | Clinical trial to evaluate efficacy and safety of Amla Extract (AMX160) in patients with Dyslipidemia | Project No. AN-03ASE
0115H2-SYN02
Ver.01, Dt: 01-01-15 |
|----------------------------------------------------------------------------------|-------------------------------------------------------------------------------------------------------|--------------------------------------------------------------|

not be included in the Per Protocol efficacy analysis while all the patients (including those with deviations and violations) will be considered for modified Intention To Treat efficacy analysis if they have completed visit 3 (week 4) with laboratory evaluation. All the subjects who have been dispensed study medication and have completed visit 3 (week 4) will be considered for safety evaluation.

Neither the investigator nor Arjuna Natural Extracts Limited will alter this study protocol. Amendments should be made only in exceptional cases once the study has started. Any change in the protocol should be approved by IEC / IRB, wherever necessary before implementation.

## 9 Study Treatment

### 9.1 Dosing schedule

Patients will be instructed to take one capsule of Amla Extract (AMX160) 500mg of M/s Arjuna Natural Extract Limited Kerala or matching placebo twice daily (morning and evening) after meals.

### 9.2 Supply and administration of Test Product

The study medications will be labelled and supplied by M/s Arjuna Natural Limited, Kerala. The study medications will be manufactured following all the relevant regulations. Matching placebo capsules will be used as reference product. All supplies will be stored in accordance with the manufacturer's instructions separately from normal hospital / practice stocks. The study medications will be provided in a total of 3 containers, each containing 66 capsules of either Amla Extract (AMX160) or placebo. (56 capsules will be used during 28 day period and 10 extra capsules will be given for 5 day buffer period during each visit). The patients will be given one container of study medication during visit 2 (Day 0), 3 (Day 28) and 4 (Day 56).

### 9.3 Dose modification for Test Product toxicity

No dose modification of the study medication will be allowed during the study.

### 9.4 Assessment of compliance for dosing

The patients will be asked to bring the container of the study medication on every follow-up visit and compliance for dosing will be assessed by medication count by study personnel out of the sight of the patient.

|                                                                                  |                                                                                                       |                                                              |
|----------------------------------------------------------------------------------|-------------------------------------------------------------------------------------------------------|--------------------------------------------------------------|
| [figure not shown] | Clinical trial to evaluate efficacy and safety of Amla Extract (AMX160) in patients with Dyslipidemia | Project No. AN-03ASE
0115H2-SYN02
Ver.01, Dt: 01-01-15 |
|----------------------------------------------------------------------------------|-------------------------------------------------------------------------------------------------------|--------------------------------------------------------------|

## 9.5 Possible drug interactions

This is a food supplement. No drug interactions are known for this product.

## 9.6 Concomitant therapy

Patients will not be permitted to take any medication (allopathic or herbal preparation) affecting lipid levels in a concomitant manner. Further, the concomitant use of medications for the treatment of other concomitant diseases, not known to interact with study medication would be permitted as deemed necessary by the investigator. A list of all the concomitant medications taken by the patient would be recorded in the Case Report Form (CRF).

## 9.7 Blinding procedures

This is a double-blind study. To maintain blindness of study treatments, placebo capsules resembling in every manner to Amla Extract (AMX160) 500mg Capsule will be used. Both the study medications will be coded centrally with randomization numbers as per the computer generated block randomization schedule. Sealed envelopes / scratch cards will be provided to the investigators by the sponsor (one each for each randomization number) indicating the randomization number and the test product contained therein. The sealed envelopes / scratch cards will be kept by the investigator in a safe but accessible place should the need for breaking the blinding medication code arises in an emergency.

## 9.8 Unblinding procedures

The sealed envelope / scratch cards containing the test product details (randomization number and study test product name) may be opened only if knowledge of the treatment regimen can influence or assist with medical management of the patient in an acute emergency. Every effort must be made to contact the sponsor before breaking the blinding code. If it is not possible to contact the sponsor and the situation is an emergency, the investigator may break the blinding code and contact the sponsor as soon as possible. The date, time and reason for breaking the code will be documented in the CRF. Patient will be discontinued from the trial once the blinding code is broken. Opened as well as unopened code envelopes / scratch cards should be returned to the sponsor at the end of the study.

## 10 Adverse Events

### 10.1 Description of adverse events

Amla Extract (AMX160) is an extract of Amla fruits and is well tolerated. No adverse events have been reported with the use of the product till now in various clinical

|                                                                                  |                                                                                                       |                                                              |
|----------------------------------------------------------------------------------|-------------------------------------------------------------------------------------------------------|--------------------------------------------------------------|
| [figure not shown] | Clinical trial to evaluate efficacy and safety of Amla Extract (AMX160) in patients with Dyslipidemia | Project No. AN-03ASE
0115H2-SYN02
Ver.01, Dt: 01-01-15 |
|----------------------------------------------------------------------------------|-------------------------------------------------------------------------------------------------------|--------------------------------------------------------------|

studies conducted earlier in patients with dyslipidaemia. Patients using Amla Extract may develop abdominal pain, nausea, fever or vomiting.

## 10.2 Procedures to evaluate an adverse event

### 10.2.1 Definitions

Adverse Event following immunization (AEFI): Any untoward medical occurrence which follows usage of study medication and which does not necessarily have a causal relationship with the usage of the medication. The adverse event may be any unfavourable or unintended sign, abnormal laboratory finding, symptom or disease.

#### Serious Adverse Events (SAEs):

Any untoward medical occurrence that at any dose:

1. Results in death,
2. Is life-threatening,
3. Requires inpatient hospitalization or prolongation of existing hospitalization,
4. Results in persistent or significant disability/incapacity
5. Is a congenital anomaly/birth defect, or
6. Requires intervention to prevent permanent impairment or damage

### 10.2.2 Adverse Events Recording

Adverse events will be elicited using the open question - Have you noticed any change in your health since your last visit? Events involving adverse drug reactions, illnesses with onset during the study or exacerbation of pre-existing illnesses should be recorded.

All observed or volunteered adverse events regardless of treatment group or suspected causal relationship to the study test products will be recorded on the adverse event page of the CRF. Safety data including adverse events will be tabulated for clinical review.

For all adverse events, the Investigator must pursue and obtain information adequate both to determine the outcome of the adverse event and to assess whether it meets the criteria for classification of a serious adverse event requiring immediate notification to the Sponsor's representative / medical expert.

Follow-up of the adverse event, even after the date of therapy discontinuation, is required if the adverse event or its sequel persist. Follow-up is required until the event or its sequel resolve or stabilises at a level acceptable to the Investigator and the study monitor.

|                                                                                  |                                                                                                       |                                                              |
|----------------------------------------------------------------------------------|-------------------------------------------------------------------------------------------------------|--------------------------------------------------------------|
| [figure not shown] | Clinical trial to evaluate efficacy and safety of Amla Extract (AMX160) in patients with Dyslipidemia | Project No. AN-03ASE
0115H2-SYN02
Ver.01, Dt: 01-01-15 |
|----------------------------------------------------------------------------------|-------------------------------------------------------------------------------------------------------|--------------------------------------------------------------|

All the adverse events will be documented in the respective CRFs including

1. Type of adverse event
2. Date of onset
3. Severity
4. Treatment given
5. Association or relationship to the study medication
6. Date of resolution
7. Duration
8. Outcome
9. Whether the adverse event is serious or not

The SAE will be recorded in an additional ‘Serious Adverse Event Reporting Form’. The SAE will be reported to the Sponsor’s representative / medical expert and to the Ethics Committee that has given approval to the study Protocol as per the applicable guidelines.

The Principal Investigator must report all serious and unexpected adverse events to the Sponsor’s representative / medical expert and to the Ethics Committee that has given approval to the study Protocol at that centre within 24 hours of the occurrence. The report of SAE of death, after due analysis shall be forwarded by the Investigator to the Chairman of Ethics Committee and the Head of the Institution where the trial has been conducted within 10 calendar days of occurrence of SAE of death. The report of SAE other than death, after due analysis shall be forwarded to the Chairman of Ethics Committee and the Head of the Institution where the trial has been conducted within 10 calendar days of occurrence of SAE.

Sponsor’s representative / medical expert will forward report of SAE of death occurring in the clinical trial, after due analysis to the Chairman of the Ethics Committee and the Head of the Institution where the clinical trial has been conducted within 10 calendar days of occurrence of the SAE of death. The report of the SAE other than death, after due analysis, will be forwarded by the Sponsor’s representative / medical expert to the Chairman of the Ethics Committee and the Head of the Institution where the clinical trial has been conducted within 10 calendar days of occurrence of the SAE other than death. Sponsor’s representative / medical expert will also communicate any unexpected SAE occurring during the clinical trial to other Investigator(s) participating in the study.

For all serious adverse events, the Investigator is obliged to pursue and provide information as requested by the study monitor/ Sponsor’s representative or Sponsor’s medical expert in addition to that in the CRF. In general, this will include a description of the adverse event in sufficient detail to allow for a complete medical assessment of the case and independent determination of possible causality. In the case of a subject’s death, a summary of available autopsy findings must be submitted

|                                                                                  |                                                                                                       |                                                              |
|----------------------------------------------------------------------------------|-------------------------------------------------------------------------------------------------------|--------------------------------------------------------------|
| [figure not shown] | Clinical trial to evaluate efficacy and safety of Amla Extract (AMX160) in patients with Dyslipidemia | Project No. AN-03ASE
0115H2-SYN02
Ver.01, Dt: 01-01-15 |
|----------------------------------------------------------------------------------|-------------------------------------------------------------------------------------------------------|--------------------------------------------------------------|

as soon as possible by the Investigator. The Investigator should ensure that information on such cases reported by telephone or other means and information entered in the CRF are accurate and consistent.

#### Discontinuation of the study due to Adverse Events

The reason for a subject discontinuing from the study will be recorded in the CRF. A discontinuation occurs when an enrolled subject ceases participation in the study, regardless of the circumstances, prior to the completion of the study. A discontinuation must be reported immediately to the sponsor if it is due to a serious adverse event. The final evaluation as required by the Protocol will be performed at the time of study test product discontinuation if medically acceptable or as soon as possible after that. The Investigator will record the reason for study discontinuation and, if possible, provide or arrange for appropriate follow-up and document the cause of the subject's condition.

The association of the adverse events to the study medication can be ascertained by WHO criteria as mentioned below:

| Causality term              | Assessment criteria*                                                                                                                                                                                                                                                                                                                                                                                                                                                                                          |
|-----------------------------|---------------------------------------------------------------------------------------------------------------------------------------------------------------------------------------------------------------------------------------------------------------------------------------------------------------------------------------------------------------------------------------------------------------------------------------------------------------------------------------------------------------|
| Certain              | 
 
• Event or laboratory test abnormality, with plausible time relationship to test product intake
 
• Cannot be explained by disease or other drugs
 
• Response to withdrawal plausible (pharmacologically, pathologically)
 
• Event definitive pharmacologically or phenomenologically (i.e. an objective and specific medical disorder or a recognized pharmacological phenomenon)
 
• Rechallenge satisfactory, if necessary
 
 |
| Probable/
Likely | 
 
• Event or laboratory test abnormality, with reasonable time relationship to test product intake
 
• Unlikely to be attributed to disease or other drugs
 
• Response to withdrawal clinically reasonable
 
• Rechallenge not required
 
                                                                                                                                                                                                 |
| Possible             | 
 
• Event or laboratory test abnormality, with reasonable time relationship to test product intake
 
• Could also be explained by disease or other drugs
 
• Information on test product withdrawal may be lacking or unclear
 
                                                                                                                                                                                                                   |
| Unlikely             | 
 
• Event or laboratory test abnormality, with a time to test product intake that makes a relationship improbable (but not impossible)
 
• Disease or other drugs provide plausible explanations
 
                                                                                                                                                                                                                                                       |

|                                                                                  |                                                                                                       |                                                              |
|----------------------------------------------------------------------------------|-------------------------------------------------------------------------------------------------------|--------------------------------------------------------------|
| [figure not shown] | Clinical trial to evaluate efficacy and safety of Amla Extract (AMX160) in patients with Dyslipidemia | Project No. AN-03ASE
0115H2-SYN02
Ver.01, Dt: 01-01-15 |
|----------------------------------------------------------------------------------|-------------------------------------------------------------------------------------------------------|--------------------------------------------------------------|

|                                         |                                                                                                                                                                                                         |
|-----------------------------------------|---------------------------------------------------------------------------------------------------------------------------------------------------------------------------------------------------------|
| Conditional/
Unclassified    | 
 
• Event or laboratory test abnormality More data for proper assessment needed, or
 
• Additional data under examination
 
                        |
| Unassessable/
Unclassifiable | 
 
• Report suggesting an adverse reaction Cannot be judged because information is insufficient or contradictory Data cannot be supplemented or verified
 
 |

\* All points should be reasonably complied with

The assessment of intensity/severity will be determined based on the investigator's clinical judgment using the following definitions:

Mild: An event that is easily tolerated by the patient, causing minimal discomfort and not interfering with everyday activities.

Moderate: An event that is sufficiently discomforting to interfere with normal everyday activities.

Severe: An event that prevents normal everyday activities.

Note: severity is not the same as 'seriousness', which is defined in SAE above

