## 6.2 Exclusion Criteria

1. Patients with more than 2 of the following risk factors -
  - Cigarette smoking
  - Hypertension (BP >140/90 mmHg or on antihypertensive medication)
  - Family history of premature CHD (CHD in male first degree relative <55 years; CHD in female first degree relative <65 years)
  - Age (men >45 years; women >55 years)
2. Patients with uncontrolled cardiovascular disease or advanced atherosclerosis (e.g. history of stroke, myocardial infarction, life-threatening arrhythmia, or coronary revascularization within the preceding 6 months; unstable angina; congestive heart failure; known or suspected clinically significant valvular heart disease or uncontrolled hypertension (>160/100 mm of Hg or use of antihypertensive medications, dose of which is not stable in the last one month))
3. Patients with very high triglyceride levels i.e. > 500 mg/dL
4. Patients with FBS more than 150 mg/dL, using insulin, glitazones. Patients using other hypoglycaemics, dose of which is not stable in last one month
5. Pregnancy, lactation and female patients not using acceptable contraceptive measures (double barrier methods, oral or injectable hormonal contraceptives or surgical sterilization)
6. Patients with hepatic impairment (SGOT or SGPT levels > 3 Upper Limit of Normal (ULN)) or renal impairment (serum creatinine  $\geq$  2.0 mg/dl)
7. Patients with any other severe systemic illness and in the opinion of the investigator would be noncompliant with the visit schedule or study procedures
8. Patients with known history of hypersensitivity to amla or any product containing amla extract
9. Patients with continuing history of alcohol and / or drug abuse.
10. Patients with any other serious concurrent illness or malignancy.
11. Participation in another clinical trial in the past 3 months

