## **7.2 Assessment of Safety**

The safety of the study medication will be assessed by recording the adverse events occurring during the entire course of the study, as mentioned in detail in “Adverse Events” section of the protocol. All observed (during general and physical examination of patients or in the laboratory parameters) or volunteered adverse events regardless of suspected causal relationship to the study test product will be recorded on the adverse event page of the CRF. ECG of all the patients will be done at the screening and at the end of the study.

|                                                                                  |                                                                                                       |                                                              |
|----------------------------------------------------------------------------------|-------------------------------------------------------------------------------------------------------|--------------------------------------------------------------|
| [figure not shown] | Clinical trial to evaluate efficacy and safety of Amla Extract (AMX160) in patients with Dyslipidemia | Project No. AN-03ASE
0115H2-SYN02
Ver.01, Dt: 01-01-15 |
|----------------------------------------------------------------------------------|-------------------------------------------------------------------------------------------------------|--------------------------------------------------------------|

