### Overall tolerability evaluation:

The overall tolerability to study medication will be evaluated at the end of study as per the following criteria:

| Grade     | Description                                                                                                                       |
|-----------|-----------------------------------------------------------------------------------------------------------------------------------|
| Excellent | No adverse event                                                                                                                  |
| Good      | Mild adverse event(s) reported which subsided with or without medication and did not necessitate stoppage of study medication     |
| Fair      | Moderate adverse event(s) reported which subsided with or without medication and did not necessitate stoppage of study medication |
| Poor      | Severe or serious adverse event(s) which necessitated stoppage of study medication                                                |

The safety endpoints would be:

- Local and systemic adverse events reported during the study
- Serious adverse events reported during the study
- Overall tolerability evaluation at the end of study

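### The only adverse event severity scale rests on discomfort and everyday activities, so a symptom-free, non-serious laboratory abnormality fits only Mild, whatever its size

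*Protocol*

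**What the plan says.** **What counts as an adverse event.** Protocol section 10.2.1 states: "The adverse event may be any unfavourable or unintended sign, abnormal laboratory finding, symptom or disease". Section 7.2 requires recording of "All observed (during general and physical examination of patients or in the laboratory parameters) or volunteered adverse events". ECG is named in neither sentence. The causality table in section 10.2.2 also treats laboratory abnormalities as things to be assessed alongside clinical events.

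**How severity is graded.** The rule stands after the causality table in section 10.2.2: "The assessment of intensity/severity will be determined based on the investigator's clinical judgment using the following definitions". There are three classes:

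- The lowest class is worded "Mild: An event that is easily tolerated by the patient, causing minimal discomfort and not interfering with everyday activities".
- The middle class, Moderate, asks for discomfort strong enough to disturb the patient's ordinary daily life.
- The highest class is worded "Severe: An event that prevents normal everyday activities".

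A note then separates severity from seriousness. Severity is one of the items to be documented in the CRF for every event.

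**Where severity is used.** Overall tolerability is one of three safety endpoints in section 7.2, beside adverse events and serious adverse events. Its Good grade reads "Mild adverse event(s) reported which subsided with or without medication and did not necessitate stoppage of study medication". Fair has the same conditions for moderate events. Poor needs a severe or serious event that made stopping the study medication necessary. Excellent means no adverse event.

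**Numeric limits.** The liver-enzyme limit "SGOT or SGPT levels > 3 Upper Limit of Normal" and the creatinine limit in section 6.2 decide eligibility only. Section 7.2 has QT and corrected QT noted, without a threshold.

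**The concern.** The protocol brings laboratory abnormalities into the adverse event record and then grades them on a scale made for symptoms. Nothing in that scale refers to how far a value lies from normal. A liver enzyme, creatinine or blood-count abnormality that the patient does not feel neither disturbs nor prevents everyday activities, so it meets neither of the two higher definitions.

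Liver safety is close to the trial's purpose. Section 1 argues for safer alternatives by pointing to the side effects of existing lipid-lowering drugs, hepatitis among them. If a marked silent rise in transaminases carries the same grade as a trivial one, a table of adverse events by severity can look reassuring for reasons unrelated to the product. The trial is also multicentre. Without a size criterion, some investigators will follow the wording and others will improvise, so grades may not be comparable between sites.

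The investigator assigns this grade on the CRF under the protocol's definitions, so the gap does not belong to the statistical analysis plan.

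**Working it through.** The protocol states no figure to reproduce. The check sets the passages against each other.

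**Step 1. Is a laboratory abnormality an adverse event?** Yes, explicitly, under sections 10.2.1 and 7.2. An ECG finding is not named. It enters only if read as an unfavourable or unintended sign; the ECG also has a row in the laboratory schedule of section 7.3.

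**Step 2. Which severity class can a symptom-free abnormality meet?**

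| Class | What the definition needs | Met by a symptom-free abnormality? |
|---|---|---|
| Mild | easily tolerated, minimal discomfort, no interference | yes |
| Moderate | discomfort that interferes with activities | no |
| Severe | activities prevented | no |

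The size of the abnormality enters no row. As an invented example, a patient enters with SGPT just below 3 times the upper limit of normal, which section 6.2 allows, has 10 times that limit at Week 12 and feels well. On the wording this fits only Mild, as a rise to just above 3 times would.

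**Step 3. Is there another scale elsewhere?** No. The numeric limits in section 6.2 serve eligibility only, and no threshold is attached to the QT readings.

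**Step 4. What happens in the tolerability grades?** Under sections 4.1.4 and 7.3, the safety laboratory tests are taken at screening and at Week 12 only. Under section 8, tolerability is graded at the Week 12 visit, when that blood is drawn. Two gaps follow:

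- A non-serious abnormality first seen at Week 12 is not Excellent, because an event exists. It is not Good or Fair, because it cannot be shown at that visit to have subsided. It is not Poor, because no stoppage was made necessary.
- A non-serious Mild or Moderate event that led to stoppage is not Good or Fair, which exclude stoppage, and not Poor, which needs a severe or serious event.

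So Mild does not simply become Good. Nor would a higher severity grade place the Week 12 finding: graded Severe without stoppage, it still fits no class.

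**Step 5. Can the effect be sized?** Only by assumption. Suppose a fraction p of an arm has a marked silent abnormality. The chance of at least one case among n patients is 1 − (1 − p)^n.

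| Assumed p | n = 49 (randomised) | n = 44 (section 14.1, before the dropout allowance) |
|---|---|---|
| 1% | 39% | 36% |
| 2% | 63% | 59% |
| 5% | 92% | 90% |

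The expected counts in 49 are 0.49, 0.98 and 2.45. These figures show how likely it is that the question arises. They do not measure a bias, and the rates are not from the protocol.

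**The case against.** The strongest reply is that laboratory safety data do not depend on the severity grade. Section 4.3 repeats laboratory tests and ECG at Week 12 to assess safety and fixes the screening values as baseline. Section 10.2.2 tabulates safety data, and section 14.4.3 analyses safety. An extreme SGPT would be visible as a value and counted as an adverse event at any grade. Summaries of shifts or threshold crossings may well be in a statistical analysis plan that is not at hand. This stands. A reader might infer that the trial cannot show an organ-toxicity signal or a difference between arms; the documents do not support that.

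Second, grading is by clinical judgment, and the seriousness criteria include life-threatening events and those needing intervention to prevent permanent damage. A reader might infer that every silent abnormality must end up as Mild however extreme. That is too absolute. An investigator may depart from the wording, and a dangerous case can be reported as serious. But judgment is tied to the listed definitions, and the protocol itself says that severity and seriousness differ. Marked but non-serious abnormalities therefore remain without a suitable grade.

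Third, ECG findings are not named as adverse events. To state outright that they are goes beyond the text. The laboratory point does not need them.

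Fourth, the tolerability endpoint is not simply biased towards Good, as Step 4 shows. Its difficulty lies in the subsided and stoppage conditions, and a numeric laboratory grade alone would not cure it.

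**Conclusion.** The point holds in a limited form. The protocol makes abnormal laboratory findings adverse events and offers one severity scale on which a symptom-free, non-serious finding fits only Mild. The same applies to an ECG finding if it is recorded as an adverse event. The severity grade therefore cannot separate a marked silent abnormality from a trivial one and leans towards good tolerability. The stated rule produces an unsuitable grade, so this is more than a missing detail.

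The conclusion assumes that investigators apply the definitions as written. The consequence is confined to the adverse event severity grade and tables; raw laboratory values and seriousness reporting can still show the signal. No sample size, analysis set or efficacy conclusion changes, and no numerical bias can be derived from the documents. The gaps in the tolerability grades are a related but separate inconsistency. The point is worth correcting because the change is cheap.

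**What to change.** In section 10.2.2, keep the three definitions for clinical events and add one paragraph. It should state that laboratory findings, and ECG findings recorded as adverse events, are graded by size on one named published toxicity scale rather than by effect on everyday activities, and that this grade is used in the adverse event severity tables. It should also say whether ECG abnormalities count as adverse events.

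Separately, reconcile the four tolerability grades in section 7.2 and on the tolerability form in the appendix with the laboratory schedule in section 7.3 and the Week 12 visit in section 8. Every patient should fall into exactly one grade, including those with a finding first seen at Week 12 and those with a non-serious Mild or Moderate event that led to stoppage. How this is resolved is for the sponsor.

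The cost is a paragraph, a derived grade from central-laboratory and ECG values already collected, and a revised tolerability form. No new samples or visits are needed. The downside is that some events will be graded less favourably than under the present wording.
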